## Results

Forty-three groups, formed from 17 health care divisions at companies or communities across the country, were randomly assigned to a control arm (21 groups) or an intervention arm (22 groups) between March 2007 and February 2008. Figure 2 shows the flow of recruitment of study subjects through annual health checkups. Approximately 230, 000 individuals (male 85%) underwent health checkups by those 43 groups in 2006. Among them, 14,473 subjects (7494 in the control and 6979 in the intervention arm) met the inclusion criteria and received an invitation letter to participate in the study. As a result 1643 subjects from the control and 1491 subjects from the intervention arm consented to participate. Finally, 2897 subjects were enrolled, with 1524 in the control and 1336 in the intervention arm. The overall consent rate of the study was approximately 20% with no difference between the study arms. Among the 2897 subjects, 57 subjects (20 in the control and 37 in the intervention arm) were enrolled with CPG of 118-143 mg/dL 6.6-7.9 mmol/L). As shown in Figure 2, those subjects are not included for the main outcome analysis. The remaining 1504 in the control and 1336 in the intervention arm will be followed up for the development of diabetes (primary outcome). The median (interquartile range) of the group size in the control arm before and after screening for eligibility was 301 (200-442) and 61 (35-88), respectively and those in the intervention arm was 313 (158-587) and 60 (41-94), respectively. There is no difference in group size between arms. In one group in the control and two groups in the intervention arm no participants were enrolled with FPG. Those three groups were not included in the calculation of cluster size. The number of company settings, community settings, and mixed settings in the intervention arm were 16, 3, and 1, respectively. The number of company settings, community settings, and mixed settings in the control arm were 15, 3, and 2, respectively. There were no differences between the arms in the characteristic of the participants in terms of age, sex ratio, FPG levels, BMI, and the prevalence of obesity (Table 2). No difference was found in the prevalence of the Metabolic Syndrome, either (Table 3). All follow-up data will be collected by winter 2012.

**Figure 2 F2:**
[figure not shown]
Flowchart of participant recruitment and trial design: main scheme (n=2840).

**Table 2 T2:** Participant characteristics by randomized intervention assignment

**Variables**	**Control arm**	**Intervention arm**
	(n=1504)	(n=1336)
Age, years	49 (44–54)	49 (44 – 55)
Male,%	85.0	83.8
Body mass index, kg/m^2^	24.0 (22.3 – 25.8)	24.2 (22.3 – 26.3)
WRPO criteria*		
Underweight (less than 18.5 BMI),%	2.1	1.8
Normal (18.5-22.9 BMI),%	33.2	31.1
Overweight (23.0-24.9 BMI),%	28.4	28.1
Obesity I (25.0-29.9 BMI),%	32.0	33.7
Obesity II (Over 30.0 BMI),%	4.3	5.4
Systolic blood pressure, mmHg	125 (114 – 136)	125 (116 – 135)
Diastolic blood pressure, mmHg	80 (71 – 87)	79 (72 – 87)
Total cholesterol, mmol/l	5.4 (4.9 – 6.0)	5.5 (4.8 – 6.1)
HDL-cholesterol, mmol/l	1.5 (1.3 – 1.8)	1.5 (1.2 – 1.8)
Triglyceride, mmol/l	1.3 (0.9 – 1.9)	1.3 (0.9 – 1.8

Values are median (interquartile range or percentage. * The subjects were categorized into following groups based on the WHO West Pacific Regional Office (WPRO) criteria; less than 18.5 BMI, as “Underweight”, 18.5 to 22.9 as “Normal”, 23.0 to 24.9 as “Overweight”, 25.0 to 29.9 as “Obese I” and over 30.0 BMI as “Obese II”.

**Table 3 T3:** Components of metabolic syndrome by randomized intervention assignment and sex

**Variables**	**Control arm**				**Intervention arm**			
	**Men**		**Women**		**Men**		**Women**	
	**(n=1279**		**(n=225)**		**(n=1119)**		**(n=217)**	
1. BMI ≥ 25 kg/m^2^	479	37.5%	67	29.8%	456	40.8%	66	30.4%
2. Hypertension	580	45.3%	75	33.3%	514	45.9%	66	30.4%
3. TG ≥ 150 mg/dl	429	33.5%	30	13.3%	360	32.2%	29	13.4%
4. HDL<40 mg/dl in men, <50 mg/dl in women	77	6.0%	27	12.0%	76	6.8%	24	11.1%
5. Hyperglycemia	1279	100.0%	225	100.0%	1119	100.0%	217	100.0%
Risk factors of metabolic syndrome								
1 factor	365	28.5%	99	44.0%	299	26.7%	97	44.7%
2 factors	416	32.5%	71	31.6%	359	32.1%	66	30.4%
≥3 factors	496	38.8%	55	24.4%	459	41.0%	53	24.4%

Data are number or percentage. Five subjects were excluded from the analyses because of missing data except for fasting plasma glucose.

## Discussion

We have launched this J-DOIT1 trial to test whether goal-focused lifestyle support delivered by healthcare providers via the telephone is feasible and effective for preventing or delaying the development of T2DM in high-risk individuals. Statutory health checkup programs, provided annually by public medical care insurance, would offer significant advantages for carrying out this study. Thus, for the recruitment of study subjects and their follow-up, biochemical and anthropometric data are all obtained from health checkup sites.

### Cluster randomization

In recently reported lifestyle intervention studies, both individual randomization and cluster randomization [42,43] have been used. The cluster randomization design has the advantages of administrative convenience, ease of obtaining the cooperation of investigators, enhancement of subject compliance, and avoidance of treatment contamination. Since study subjects in this trial are employees of the same workplaces or inhabitants of the same communities, we chose cluster randomization to avoid diluting the effect of the intervention. The contamination could occur with individual randomization e.g. by control subjects receiving part of the intervention in a shared environment. Generally, cluster randomized trials, are susceptible to a range of methodological problems including selection bias [18]. Selection bias can be avoided by recruiting and enrolling the study subjects into the study before the groups are allocated to the study arms [44]. In our study design, however, the study subjects were recruited after the clusters were randomly allocated to the intervention or control arm. The reason for nor recruiting and enrolling subjects before randomization was that it was not practical due to the nature of the intervention, in which it takes too long to recruit individuals first. The individuals or the recruiters were not blinded to the allocation status. Careful attention should be paid to the likelihood of selection bias in our sample based on the cluster sizes between the two arms and comparison of the participants.

### Telephone-delivered interventions

Structured intensive lifestyle modification can prevent T2DM in hospital and clinic settings [45-47], and primary healthcare settings [48]. To target young and middle-aged people, who are busy with work, this study employs a non face-to-face intervention using the telephone. Telephone-delivered intervention has a greater accessibility and potential availability of participants for the interview than face-to-face provided support. They facilitate, in a cost-effective manner [37], repeated contact and support for the participant necessary to promote maintenance of physical activity and diet. Thus telephone counseling would make it possible to deliver lifestyle intervention widely, at a low cost, but in a personalized way. There has been increasing interest in lifestyle support using the telephone [49-53]. However, it is unknown whether telephone-delivered support for lifestyle modification by healthcare providers is a feasible and effective way to prevent or delay the development of T2DM. If it is proved effective, lifestyle coaching by healthcare providers using telephone would be a promising tool for reducing the incidence of diabetes.

### Retention

The final sample size (2840 participants) would provide >80% power to detect a 50% reduction in the rate of development of T2DM among participants assigned to the lifestyle intervention with a 5% level of significance (two-sided), after no adjustment for losses in follow-up. The follow-up of participants is scheduled to finish in March 2012. Retention of participating health checkup facilities and subjects are critical for the success of this study. Drop-out rates are generally high in lifestyle programs conducted in primary healthcare clinical settings. To secure enough samples for analysis, participants are encouraged to attend an annual health checkup through a letter from the lifestyle support center. The lifestyle support center gives safety advice to prevent sport injuries which could lead to dropping out of the study.

### BMI and the Metabolic Syndrome

We included not only overweight and obese subjects, but also subjects with a BMI of < 23 kg/m^2^. Therefore, the BMI ranged widely from <18.5 to >30 in our study subjects with an average value of 24.3. Only 39.0% of men and 30.1% of women had a BMI of ≥25 kg/m^2^. Compared with western populations, obesity is less common in our general population [54]. It has also been reported that about 25% of subjects with impaired glucose tolerance have normal or even underweight categories of BMI [36]. It seems that the relationship between BMI and the risk of diabetes is not so straightforward in our population. Thus, we did not set eligibility criteria in terms of BMI. It would be of interest to study the incidence of diabetes and see what strategies are effective to prevent the development of diabetes in those with a lower BMI. In 2008, the concept of the Metabolic Syndrome was introduced in the health checkup program in our country [55]. Mukai et al. suggested that the Metabolic Syndrome significantly increased the risk of incident T2DM, irrespective of the presence or absence of impaired fasting glucose(IFG), and is therefore a valuable tool to identify individuals at high risk of T2DM in the general population in Japan [56]. In this study, we found 39.8% of men and 24.8% of women have ≥3 risk factors for cardiovascular diseases, suggesting they have the Metabolic Syndrome. The present study would allow us to compare the incidence of T2DM in IFG subjects with or without the Metabolic Syndrome in a subanalysis.

### Limitations

This study has several potential limitations. One is that we identified high risk subjects using fasting plasma glucose. We will follow them as to the development of diabetes using fasting plasma glucose determined at annual health checkups and a questionnaire. We do not add any other biochemical examinations such as the oral glucose tolerance test. Therefore, we may miss diabetic subjects having normal fasting but elevated 2 h plasma glucose levels [57-59]. We may also miss subjects with IGT, IFG and IGT, both associated with a substantially increased risk of developing diabetes, are considered to be of a different entity. In the majority of populations thus far studied, IGT is more prevalent than IFG. Thus, we must be careful in interpreting results. It is possible that the efficiency of identifying high-risk subjects will be increased by combining FPG and HbA1c data [60]. This study used results obtained in 2006 annual health checkups as baseline data. At that time, only 58.5% of participating checkup sites included the measurement of HbA1c as a health checkup item. Second, the present study lacks information on the use of drugs, such as fibrate, nicotinic acid, and fish oil, which affect the metabolism of HDL-cholesterol and triglycerides. This may have led us to underestimate the prevalence of the Metabolic Syndrome. Third, participants were predominantly from workplaces. We did not succeed in recruiting more participants from communities. Since men outnumber women in many workplaces in Japan, the study population was predominantly male. This bias may limit the generalizability of our results.

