### Randomization

For cluster randomization, the groups were randomly allocated to either an intervention (n=22) or a control (n=21) arm. Randomization was performed 3 times according to 3 recruitment periods (March to April, May to June, and July to August in 2007). When two or more groups were made from one health care division, they were allocated to each of the arms within the health care division. Some small groups were pooled with others. Allocation was carried out using stratified randomization with seven strata of companies or communities in the first period, five strata in the second period, and three strata in the third period. A randomization list was prepared by an independent statistician using the SAS PLAN procedure with seed = 4989. This procedure was conducted using SAS version 9.1 (SAS Inc., Cary, NC, USA). Simple randomization was performed with 2 levels of treatment. The groups were notified of their allocation status before study subjects were recruited. The subjects were notified of their allocation status when they were recruited.

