### Health checkups

Guidelines for health check implementation were announced in 2004 based on the Health Promotion Law. In 2006 mandatory items to be checked included 1) anamnesis of past history including history of medication and smoking, 2) subjective and objective symptoms, 3) body height and weight, 4) Body Mass Index (BMI), calculated as body weight (kg) divided by square of body height (m^2^), 5) blood pressure, 6) serum alanine aminotransferase, asparate aminotransferase and gamma glutamyltranspeptidase, 7) serum triglycerides, HDL cholesterol and LDL cholesterol, 8) fasting plasma glucose, and 9) urinalysis. At health checkup sites anthropometric measurements were done by public health nurses or industrial nurses. Height was measured in the standing position by public health nurses or industrial nurses. Weight was measured without shoes or heavy clothes to the nearest 0.1 kg using standard calibrated scales. Systolic and diastolic blood pressure values were measured in the sitting position [21]. Blood was withdrawn after 8 hours of fasting and analyzed with standard methods in clinical laboratories under the nationally certified laboratory management system. If blood was withdrawn from people who had not fasted, plasma glucose data was treated as casual plasma glucose and triglycerides values were omitted from the analysis. We did not perform any additional tests for this study.

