### Inclusion and exclusion criteria for study subjects

Using the 2006 year health checkups data, candidates who met the inclusion criteria were identified in each cluster. Inclusion criteria included an age of 20-65 years and impaired fasting glucose (IFG) defined as a fasting plasma glucose concentration (FPG) of 100-125 mg/dL (5.6-6.9 mmol/L). In the 2006 year health checkups, however, blood sampling was not always done in the fasting state. In those individuals where the FPG was not available, plasma glucose concentrations (casual plasma glucose, CPG) of 118-143 mg/dL (6.6-7.9 mmol/L) [22,23] were considered eligible. A CPG ≥11.1 mmol/l (200 mg/dl) indicates diabetic type of glucose tolerance according to the report of the committee on the classification and diagnostic criteria of diabetes mellitus [24,25]. A CPG is also used as the risk assessment for cardiovascular disease in Japan [26]. Exclusion criteria included diagnosed diabetes, a previous history of diabetes taking anti-diabetic agents, a HbA1c of ≥ 6.5% [27]. Women with a history of gestational diabetes could be enrolled. Physical or medical conditions that do not allow exercise, pregnancy or possible pregnancy, evidence for of type 1 diabetes mellitus, liver cirrhosis or chronic viral hepatitis (type B or type C), and use of a cardiac pacemaker were also included as exclusion criteria. We also excluded those who had already participated in other lifestyle modification programs and those who could not obtain the approval from their doctors.

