### Enrollment of the study subject

We outsourced some parts of the study works to three existing private companies (Tokio Marine & Nichido Medical Service Co., Ltd., National Education Association, INC. VISIT HEALTH Co., Ltd., and Meiji Yasuda System Technology Co., Ltd., Japan). They were all practicing healthcare services. They participate in this study as a lifestyle support center, which managed the recruitment and enrollment of study subjects and the lifestyle intervention. The lifestyle support center sent a program kit by mail to the eligible subjects in each cluster, inviting them to participate in the study. The kit included an explanation about the study’s aims and protocol, a consent form, and a questionnaire regarding lifestyle and health status. Those who consented to participate and completed the questionnaire were enrolled as study participants at the lifestyle support center, after their eligibility was checked based on their self-reported present and past health conditions and, when available, based on information from physicians in the health care divisions.

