
**Figure 1 F1:**
[figure not shown]
Telephone-delivered lifestyle modification support model: theory matrix.

**Table 1 T1:** Schedules of telephone counseling of the three lifestyle support centers

	**National Education Association INC. VISIT HEALTH**	**Meiji Yasuda System Technology**	**Tokio Marine & Nichido Medical Service**
Introduction and welcome call	In Week 1	In Month 2	In Month 3
Support calls	In Months 2, 3, 4, 7, and 10.	In Months 3, 4, 5, 6, 7, 8, 9, 10, and 11.	In Months 7 and 12
Advice sheets by mail	No	Monthly, during Month 2-12	Monthly, during Month 2-12
Feedback by graph (body weight and footsteps)	Monthly	Monthly	Monthly
The number of groups in the control/intervention arm	8/8	8/7	4/5
The number of subjects in the control	595/722	413/484	328/298

Data are n.

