### Follow-up and outcome

Participants will be followed up over a three- year period using data from an annual health checkup and a questionnaire regarding health and lifestyle. The questionnaires are mailed out to the participants from the lifestyle support center with self-addressed envelopes. If a completed questionnaire is not sent back to the lifestyle support center within two weeks, the lifestyle support center will contact the participant first by mail and then by telephone. We made a manual for this process. The primary outcome is the development of diabetes in participants whose FPG concentration is 100-125 mg/dL (5.6-6.9 mmol/L) at baseline. The development of diabetes is defined as; #1) a rise in FPG to a level equal to or greater than 126 mg/dL (7.0 mmol/L) as revealed in the follow-up annual health checkup, and #2) a diagnosis of diabetes or use of anti-diabetic drugs as reported in the annual questionnaire with confirmation by referring to medical records. Other outcomes are changes in body weight, BMI, plasma glucose, blood pressure, serum lipids, HbA1c, the percentage of subjects with the Metabolic Syndrome, lifestyle, and the development of cardiovascular diseases.

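### Baseline glucose dates from the 2006 check-up and is not re-measured at enrolment in 2007 or later, so undiagnosed diabetes that arose in between counts as incident and pulls the hazard ratio toward 1

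*Protocol article*

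**What the plan says.** **Source of baseline.** Under Inclusion and exclusion criteria, "Using the 2006 year health checkups data, candidates who met the inclusion criteria were identified in each cluster". Limitations confirms it: "This study used results obtained in 2006 annual health checkups as baseline data". That section raises the 2006 date only in connection with HbA1c availability.

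**Timing of allocation.** Results says the groups "were randomly assigned to a control arm (21 groups) or an intervention arm (22 groups) between March 2007 and February 2008". The Randomization section instead gives three rounds between March and August 2007. The two windows differ and should be reconciled, but both lie after the 2006 check-up. Randomization and the Discussion's section on cluster randomization both say that individuals were recruited after their group had been allocated.

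**Check at enrolment.** Under Health checkups: "We did not perform any additional tests for this study". Under Enrollment of the study subject, people were registered "after their eligibility was checked based on their self-reported present and past health conditions and, when available, based on information from physicians". Diagnosed diabetes is an exclusion criterion.

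**Event rule.** The primary outcome applies to people with FPG of 100-125 mg/dL at baseline and counts "a rise in FPG to a level equal to or greater than 126 mg/dL (7.0 mmol/L) as revealed in the follow-up annual health checkup", or a diagnosis or drug use reported in the questionnaire and confirmed in medical records. The article gives no rule for diabetes that began between the 2006 check-up and enrolment.

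**The concern.** A time-to-diabetes comparison assumes that everyone in the risk set is free of diabetes at time zero. Here that was shown only in 2006. Someone whose FPG rose to 126 mg/dL or more before enrolment, without a diagnosis, passes the enrolment check and is then counted at the first follow-up check-up. The intervention could not have prevented that event.

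If such events occur at the same rate in both arms, they add the same amount to each risk and move the hazard ratio toward 1, so a real benefit would look smaller and be harder to detect. Secondary changes measured from the 2006 values carry the same problem, because they include drift that preceded enrolment.

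**Working it through.** **1. The plan's own figures.** Sample size section: control incidence 4% per year, halved by the intervention, alpha 5%, power 90%, ICC 0.02, cluster size 60, dropout 30%. Follow-up is three years.

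- Freedman's formula for a hazard ratio of 0.50 gives 95 events. With hazards of 0.04 and 0.02 the three-year risks are 11.3% and 5.8%, mean 8.57%. 95 / 0.0857 is about 1109, close to the stated 1100.
- Design effect: 1 + 59 × 0.02 = 2.18, and 1100 × 2.18 = 2398.
- 2398 / 60 is about 40 clusters, and 2398 / 0.70 = 3426. The stated figures reproduce.

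**2. The gap.** The latest 2006 check-up and the earliest randomisation are about 2 to 3 months apart. From January 2006 to February 2008 is about 25 months. The gap for each person is not given. I assume g = 3 to 12 months.

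**3. Undiagnosed share.** The enrolment check removes diagnosed and reported cases. The share it misses is not given. I assume u = 50 to 100%.

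**4. Formulas.**
- Already diabetic at enrolment: q = u × (1 − 0.96^g), g in years.
- Three-year risks without gap cases: control 1 − 0.96³ = 11.53%, intervention 1 − 0.98³ = 5.88%.
- Observed risk in each arm: q + (1 − q) × risk.
- Apparent HR = ln(1 − intervention risk) / ln(1 − control risk).
- Power = Φ(|ln HR| × √(events / 2.18 × 0.2491) − 1.96), where 0.2491 = (1504/2840) × (1336/2840). Events come from 1504 and 1336 participants, or from 70% of each.

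**5. Results.**

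| Gap | Undiagnosed | q | Of 2840 | Control risk | Intervention risk | Apparent HR | Power, 30% loss | Power, no loss |
|---|---|---|---|---|---|---|---|---|
| none | – | 0 | 0 | 11.53% | 5.88% | 0.495 | 88% | 97% |
| 3 months | 50% | 0.51% | 14 | 11.98% | 6.36% | 0.515 | 86% | 95% |
| 3 months | 100% | 1.02% | 29 | 12.42% | 6.84% | 0.534 | 84% | 94% |
| 12 months | 50% | 2.00% | 57 | 13.30% | 7.76% | 0.566 | 80% | 92% |
| 12 months | 100% | 4.00% | 114 | 15.07% | 9.65% | 0.621 | 72% | 86% |

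The first row is 0.495 rather than 0.50 because halving a yearly probability is not quite halving a hazard.

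Example, last row with 30% loss: events are 1052.8 × 0.1507 + 935.2 × 0.0965 = 248.9. Then √(248.9 / 2.18 × 0.2491) = 5.33 and |ln 0.621| = 0.476. Φ(5.33 × 0.476 − 1.96) = Φ(0.58), about 72%.

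**6. Sensitivity.** With constant hazards of 0.04 and 0.02, the HR runs from 0.52 to 0.625 over the same range, and power with 30% loss falls from 87.0% to between 84.8% and 70.0%. At 12 months and 100% undiagnosed, the HR is 0.625 whether the yearly rate is 2%, 4% or 7%. An 18-month gap, which the dates also allow for some participants, gives 0.60 to 0.67.

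**The case against.** Building the trial on routine check-ups is a deliberate and disclosed choice. The enrolment check is more than bare self-report, since physicians' information was used where available. The article does not state time zero, and its dropout definition refers to check-ups after enrolment, which suggests that follow-up starts there. Such details can be left to the full protocol. Balanced dilution cannot create a false benefit.

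Much of this stands and limits the size of the point. It does not remove it: even with follow-up starting at enrolment, an unrecognised case from the gap is first seen at a follow-up check-up and meets the event rule. That follows from what the article states, not from what it omits. Balance is also not assured, because recruiters and participants knew the allocation.

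Four stronger readings are tempting, and the document does not support them:

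- **All gap cases are counted.** Diagnosed and reported cases are screened out, so 29 to 114 of 2840 is the upper bound over the 3 to 12 month range.
- **Power could fall to about 45%.** This needs the three years to run from the 2006 check-up, which would end follow-up in 2009. The Retention section schedules follow-up to March 2012.
- **The stated power above 80% is wrong.** Retention gives that figure without adjustment for losses. On that basis power is 86% or more across the assumed range.
- **The wait for the first call is part of the error.** In Table 1 the row "Introduction and welcome call" shows Week 1, Month 2 and Month 3. A start-up delay after enrolment belongs to the strategy being compared under intention to treat. The centre with the Month 3 call also mails advice sheets from Month 2.

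**Conclusion.** The point holds in a limited form. The 2006 baseline, later recruitment, absence of a re-test and event rule together count undiagnosed pre-enrolment diabetes as incident. If it is balanced between arms, a true hazard ratio of 0.50 would appear as about 0.52 to 0.62. With the plan's design effect and 30% loss, power would be about 86% to 72% instead of 88%.

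This rests on the plan's 4% yearly incidence, three years of follow-up after enrolment, and two assumed ranges that the document does not supply: a gap of 3 to 12 months and 50 to 100% of gap cases undiagnosed. Longer gaps would dilute more. If the cases are not balanced, the direction of bias is not known in advance. The estimate is affected whether or not power remains adequate, and the article does not mention it as a limitation. It should be corrected, but it does not invalidate the trial.

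**What to change.** Set these rules before the blinded final analysis:

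1. Time zero is enrolment, and no check-up dated before enrolment counts as follow-up.
2. FPG of 100-125 mg/dL in 2006 remains the entry criterion. People who later fell below 100 mg/dL stay in.
3. Where the data supplied by the divisions contain a later check-up dated before enrolment, participants with FPG of 126 mg/dL or more at that check-up leave the primary risk set, by the same rule in both arms. This uses only pre-enrolment data.
4. Exclusions are reported by arm, because enrolment dates were set after unblinded allocation.
5. Secondary changes are measured from the last pre-enrolment check-up.
6. Where only the 2006 result exists, the rule changes nothing, and the remaining dilution is stated as a limitation.
7. The two randomisation windows are reconciled.

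A sensitivity analysis that ignores events before the centre's scheduled first call, applied equally to that centre's controls, is optional.

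The cost is some wording and data handling. The divisions already had to agree to supply check-up data every year from 2006, so no new test is needed. A small number of participants and events would be lost. How many have a usable pre-enrolment check-up cannot be told from the article.
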